### Data collection

Data collection will be conducted in a structured and systematic manner to ensure the reliability and validity of the results. This process will begin with the acquisition of the necessary ethical and administrative approvals prior to any data collection activities. The study will also be registered with the Iranian Registry of Clinical Trials (IRCT20241023063481N1). To ensure data quality, all research personnel received standardized protocol training. The researcher will visit the selected health centers, explain the objectives and methodology of the study to the managers and healthcare staff, and obtain their consent to cooperate. Following this, the process of informing potential participants will begin. Assessments occur at three time points: baseline (pre-intervention), immediately post-intervention (week 8), and at a 3-month follow-up. At each stage, outcome measures (cognitive empowerment, mental vitality) are collected. To uphold the intention-to-treat principle, all participants initially randomized will be included in the final analysis. Individuals who choose to discontinue the active intervention sessions will still be invited to provide outcome data at the designated follow-up assessments (week 8 and 3 months), subject to their ongoing consent for this limited study involvement. Copies of all paper-based data collection forms are retained as study records and are available for review upon reasonable request.

### Data management and security

All data will be managed using unique participant ID codes. Paper questionnaires will undergo a double-entry process with range checks into a secure database. The final dataset will be stored on a password-protected and encrypted drive at Babol University of Medical Sciences, accessible only to the core research team. Regular backups will be performed. The full data management plan is available upon request.

### Pretest (baseline measurement)

Prior to the commencement of the intervention, a pre-test will be conducted, during which participants will complete a set of questionnaires designed to assess baseline variables related to demographic characteristics, physical and mental health status, cognitive empowerment, and mental vitality. These initial measurements will provide a foundation for comparison with post-intervention data.

### Posttest (immediate follow-up)

Upon completion of the 8-week intervention period, a posttest will be administered to evaluate the immediate effects of the intervention on the participants. This assessment will include questionnaires on cognitive empowerment and mental vitality to identify any changes in the measured outcomes. The comparison will help determine the immediate impact of the intervention.

### Follow-up (long-term evaluation)

Three months after the intervention, a follow-up evaluation will be conducted to assess the sustainability of the intervention’s effects. Follow-up data will be used to examine any lasting changes in cognitive empowerment and mental vitality. This period will be essential for determining whether the intervention has long-term benefits or if observed improvements were temporary. Throughout the data collection process, the researcher will ensure that all procedures are implemented in a standardized manner to maintain consistency across participants and measurement time points.

### Outcomes

#### Primary outcome

The primary outcome is the change in Cognitive Empowerment score from baseline to the post-intervention assessment at week 8. To measure this variable, the Ability to Recognize Cognitive Changes questionnaire will be used. This questionnaire was designed and psychometrically evaluated by Tarighat et al. [14]. The questionnaire consisted of 25 questions that assessed older adults’ ability to recognize their own cognitive changes across 8 dimensions on a 3-point scale: physical strength (5 questions), self-esteem (5 questions), spirituality (2 questions), commitment (2 questions), role performance (4 questions), situation recognition (2 questions), self-management (3 questions), and self-assessment (2 questions). The total score ranged from 25 to 75. A score of 0 to 25 indicates that older adults’ ability to recognize cognitive changes is at an unfavorable level, 25 to 50 at a relatively favorable level, and a score above 50 at a favorable level. The questionnaire’s reliability and validity have been established, demonstrating satisfactory content and construct validity alongside a Cronbach’s alpha of 0.70.

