### Sample size

The required sample size was calculated using G* Power software, based on the method described by Kazazi et al. [13]. Among the study objectives, the one requiring the largest sample was selected as the basis for estimation, specifically the evaluation of the intervention’s effect on cognitive empowerment in older adults. According to prior data, the mean (±standard deviation) of the mental status examination scores after the intervention was 28.3 ± 1.8 in the intervention group and 27.5 ± 2.1 in the control group. Using these values, the calculated effect size was 0.41. With a statistical power of 95% and an alpha level of 0.05, and assuming two repeated measurements after the intervention, the minimum required sample size was determined to be 58 participants. To account for a possible 20% attrition rate and a design effect of 1.6 due to cluster sampling, the final adjusted sample size was increased to 111 participants, resulting in 37 individuals per group.

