#### Secondary outcomes

Secondary outcomes include the change in mental vitality score at week 8 and the evaluation of effect sustainability, measured by assessing both the Cognitive Empowerment and Mental Vitality questionnaires at the 3-month follow-up time point. It will be assessed using the Subjective Vitality Scales (SVS) by Ryan and Frederick (1997). This scale has two versions at two levels: individual differences (SVS-IDL) and state (SVS-SL). SVS-IDL reflects individuals’ continuous, stable, and enduring characteristics, which are positively associated with self-actualization and self-esteem and negatively associated with depression and anxiety. SVS-IDL state differences assess state differences instead of the stable aspect. This version is negatively associated with physical pain but positively associated with autonomy support level in a specific situation.

Each version consists of seven items and is scored on a 7-point Likert scale ranging from 1 (“Not at all true for me”) to 7 (“Very true for me”). The overall score was calculated by summing the scores of all the questionnaire items. Higher scores for each version indicate higher mental vitality and vice versa. The minimum and maximum mental vitality scores for each version are 7–49. The scale score for each version is calculated separately. It is recommended to use six items and disregard item 2. In this study, we removed question 2 and considered the average of the six questions as the individual score. The content, face, and criterion validity of this questionnaire were deemed appropriate for evaluation. This scale possesses established criterion validity and good internal consistency, with a reported Cronbach’s alpha coefficient above 0.70 [13, 15].

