### Statistical methods

To assess the homogeneous distribution of confounding variables across the three groups before the intervention, the chi-square test was used for categorical variables, and one-way ANOVA was applied for continuous variables. All analyses will follow the intention-to-treat principle. Missing data (up to 14%) will be imputed using regression methods.

The primary analysis will test the superiority of the interventions on the primary outcome: change in cognitive empowerment score at week 8. To account for multiple comparisons, the significance level for the three pre-planned between-group comparisons (walking vs. control, meditation vs. control, walking vs. meditation) will be adjusted using the Bonferroni correction, resulting in a corrected alpha of 0.0167.

Changes in outcomes over time, between groups, and their interaction will be analyzed using the generalized estimating equation (GEE) model. Baseline individual and clinical variables showing significant between-group differences (e.g., age, marital status, physical activity) will be included as covariates to control for potential confounding. Analyses for secondary outcomes will be considered exploratory.

All analyses will be conducted using Stata version 17, with a two-tailed alpha level of 5% for tests not covered by the primary correction. Graphs will be generated using GraphPad Prism version 8.

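### The sample size credits two post-intervention measurements, but the primary comparison uses week 8 only, so the stated 95% power is not the power of the primary test

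*Protocol article*

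**What the plan says.** The Sample size section of the protocol article chooses as its basis the objective needing the most participants, "specifically the evaluation of the intervention’s effect on cognitive empowerment in older adults". It takes post-intervention scores of "28.3 ± 1.8 in the intervention group and 27.5 ± 2.1 in the control group" and reports that "the calculated effect size was 0.41". With 95% power and alpha 0.05, it continues: "assuming two repeated measurements after the intervention, the minimum required sample size was determined to be 58 participants". Allowances for 20% attrition and a design effect of 1.6 bring this to 111, or 37 per group.

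Data collection lists only two assessments after the intervention: week 8 and 3 months. The Primary outcome section uses the first alone: "The primary outcome is the change in Cognitive Empowerment score from baseline to the post-intervention assessment at week 8". Statistical methods agrees: "The primary analysis will test the superiority of the interventions on the primary outcome: change in cognitive empowerment score at week 8". It sets a Bonferroni alpha of 0.0167 for each of three pairwise comparisons. Secondary outcomes places the later visit elsewhere, with sustainability "measured by assessing both the Cognitive Empowerment and Mental Vitality questionnaires at the 3-month follow-up time point", and Statistical methods calls secondary analyses exploratory.

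**The concern.** The calculation counts a measurement that the primary outcome leaves out. Averaging two imperfectly correlated visits reduces the variance of a between-group comparison. A sample size that relies on that reduction does not carry over to a test at one visit. With complete data, the 3-month score adds nothing to a week-8 group contrast from a model with free group-by-time terms.

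This is the article's only power figure. A non-significant week-8 result would be read as coming from a trial with 95% power, although that figure was derived for a different number of measurements. The limitations paragraph of the Discussion concedes that power may be limited, but gives no number and does not correct the Sample size section.

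**Working it through.** **Inputs from the protocol article.** Means 28.3 and 27.5, SDs 1.8 and 2.1, effect size 0.41, power 95%, alpha 0.05, two post-intervention measurements, base size 58, attrition 20%, design effect 1.6, 37 per group (Sample size); alpha 0.0167 per comparison (Statistical methods). **Assumed, because not given:** the correlation r between visits, taken as 0.3, 0.5 and 0.7.

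**1. The plan's own figures.**
- Pooled SD = √((1.8² + 2.1²)/2) = 1.956, and d = 0.8/1.956 = 0.409. The stated 0.41 is confirmed as a standardized difference.
- 58 × 1.2 × 1.6 = 111.4. The stated 111 is confirmed.
- The base size was tried with the repeated-measures between-groups F test, noncentrality λ = N·m·f²/(1 + (m−1)r). With m = 2, two groups, r = 0.5 and 0.41 entered as Cohen's f, N is 60 and power at 58 is 94.3%. At r = 0.3, N is 54, so 58 lies between the two. For two groups, however, d = 0.41 corresponds to f = 0.205, and with that value N is 234 at r = 0.5. Under this formula, 58 is recovered only if d is entered as f.

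**2. One visit instead of two, post-only scores.** The mean of two visits has (1 + r)/2 times the variance of one. At 95% power and two-sided alpha 0.05, the standardized signal is 1.645 + 1.960 = 3.605. With one visit, power = Φ(3.605·√((1 + r)/2) − 1.960).

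**3. One visit as change from baseline.** With one common correlation, a change score has 2(1 − r) times the single-visit variance. Power = Φ(3.605·√[((1 + r)/2)/(2(1 − r))] − 1.960).

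| r | Post-only, week 8 | Change from baseline, week 8 |
|---|---|---|
| 0.3 | Φ(2.906 − 1.960) = 83% | Φ(2.456 − 1.960) = 69% |
| 0.5 | Φ(3.122 − 1.960) = 88% | Φ(3.122 − 1.960) = 88% |
| 0.7 | Φ(3.323 − 1.960) = 91% | Φ(4.291 − 1.960) = 99% |

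The change score matches the two-visit mean where 2(1 − r) = (1 + r)/2, that is at r = 0.6, and does better above that.

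**4. The primary comparison at the planned size.** Take d = 0.41 in units of the single-visit SD, 37 per group, and no allowance for dropout or design effect. Noncentrality = 0.41·√(37/2) = 1.763 on 72 degrees of freedom.
- Post-only: about 41% power at alpha 0.05 and 25% at 0.0167 (normal approximation 42% and 26%).
- Change score at alpha 0.0167: divide 1.763 by √(2(1 − r)). This gives 1.490, 1.763 and 2.277, and power of about 18%, 25% and 44% at r = 0.3, 0.5 and 0.7.

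**The case against.** The strongest reply is that the primary outcome is a change from baseline, not a post-only score. A reader might infer that the two-visit analysis is simply the easier one and that the week-8 test must fall short of it. The documents do not support that as a flat statement: with a common correlation above 0.6, the week-8 change score is the more precise of the two. This objection stands, and it limits what can be said about direction. It does not rescue the stated figure, because the Sample size section claims no benefit from baseline.

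A second reply is that the article names neither the G*Power test nor the correlation, and refers to a cited study for the method. That averaging over visits produced the 58 is therefore an inference, though the wording fits a between-groups test most naturally. This also stands. The mismatch in the number of measurements is in the text whichever test was used.

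A third reply is that the GEE model uses every visit. It does, but the named primary test is at week 8.

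Finally, a reader might take 83% to 91% as the trial's actual power, or conclude that enrolment should rise by the corresponding factor 2/(1 + r). Neither follows. Those figures isolate one assumption and accept the starting 95%, which step 1 of the working could not reproduce with 0.41 read as a standardized difference.

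**Conclusion.** The point holds as an inconsistency between sections: the stated 95% power and base size of 58 rest on two post-intervention measurements, and the primary comparison uses one. Nothing elsewhere in the article reconciles them.

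Taken alone, this moves 95% to about 83% to 91% for post-only scores, assuming r from 0.3 to 0.7. For a change score it gives 69% to 99% over the same range, assuming one common correlation. The sign of the effect for the named endpoint is therefore not proven.

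The number of measurements is also not the largest problem in the calculation. With d = 0.41 read as what it is, 37 per group gives about 25% power at alpha 0.0167 for a post-only score and about 18% to 44% for a change score, before dropout and clustering. Correcting only the number of visits would not restore 95%.

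**What to change.** In the Sample size section, remove the assumption of two post-intervention measurements. Restate the power, or the detectable difference, at 37 per group for the single week-8 change comparison. State the assumed correlation with baseline, use 0.41 explicitly as a standardized difference d, and use the alpha of 0.0167 from Statistical methods.

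The cost is one recalculation and a corrected passage. Neither enrolment nor the primary outcome has to change. The price is a less favourable stated power.

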#### Secondary outcomes

Secondary outcomes include the change in mental vitality score at week 8 and the evaluation of effect sustainability, measured by assessing both the Cognitive Empowerment and Mental Vitality questionnaires at the 3-month follow-up time point. It will be assessed using the Subjective Vitality Scales (SVS) by Ryan and Frederick (1997). This scale has two versions at two levels: individual differences (SVS-IDL) and state (SVS-SL). SVS-IDL reflects individuals’ continuous, stable, and enduring characteristics, which are positively associated with self-actualization and self-esteem and negatively associated with depression and anxiety. SVS-IDL state differences assess state differences instead of the stable aspect. This version is negatively associated with physical pain but positively associated with autonomy support level in a specific situation.

Each version consists of seven items and is scored on a 7-point Likert scale ranging from 1 (“Not at all true for me”) to 7 (“Very true for me”). The overall score was calculated by summing the scores of all the questionnaire items. Higher scores for each version indicate higher mental vitality and vice versa. The minimum and maximum mental vitality scores for each version are 7–49. The scale score for each version is calculated separately. It is recommended to use six items and disregard item 2. In this study, we removed question 2 and considered the average of the six questions as the individual score. The content, face, and criterion validity of this questionnaire were deemed appropriate for evaluation. This scale possesses established criterion validity and good internal consistency, with a reported Cronbach’s alpha coefficient above 0.70 [13, 15].

### Additional assessments

Additional baseline assessments comprise the Mini-Cog test for cognitive screening, the Tandem Gait Test for evaluating balance and gait, and a structured form to collect demographic and clinical data.

### Mini-Cog

Mini-Cog is a quick cognitive screening test for older adults, consisting of the Three-Word Recall Test and the Clock Drawing Test. The recall test involves remembering three words, while the clock test assesses executive function by having the person draw a clock showing 11:10. Scores range from 0 to 5, with 0–2 indicating potential cognitive impairment and 3–5 indicating normal cognitive function. This test is simple, fast, and effective for detecting early cognitive decline.

### Balance Test (Tandem Gait Test)

Tandem Gait Test is a simple, noninvasive test used to assess dynamic balance in older adults. It involves walking in a straight line, placing the heel of one foot directly in front of the toes of the other foot. The test is performed in a flat, unobstructed area, and safety measures are taken to prevent falls. The test results are categorized as normal or abnormal based on balance, accuracy, and stability. (Additional File 1).

### Demographic information

Demographic information includes age, gender, occupation, level of education, retirement status, marital status, number of children, whether children are dependent on you in any way, whether you are dependent on children in any way, economic status, with whom you live, number of medications used, history of chronic diseases, co-occurring chronic diseases, uncorrected disabilities, history of hospitalization in the past year, physical activity level, and self-rated health (Additional File 1). The research design management plan (Table 2) and SPIRIT diagram (Fig. 3) are presented below.

**Table 2 Tab2:** Project management plan

Stage		Tasks	Timeline	Responsibilities
1	Drafting and planning	• Designing a research proposal • Obtaining ethical approvals • Registration in the Iranian Clinical Trials System	1 month	Researcher
2	Recruitment and selection of participants	• Informing health centers • Calling for elderly women • Assessing entry criteria	2 weeks	Researcher and colleagues
3	Data collection	• Administering questionnaires (pretest) • Starting interventions • Monitoring the intervention process	1 month	Researcher and research team
4	Implementation of interventions	• Holding walking and meditation sessions • Holding meaningful conversations	1 month (8 sessions)	Researcher and facilitators
5	Post-intervention data collection	• Administering questionnaires (posttest) • Following up and collecting follow-up data	2 weeks	Researcher and research team
6	Data analysis	• Analyzing the collected data • Preparing a report of the results	1 month	Researcher and analysts
7	Dissemination of results	• Writing an article for publication • Presenting the results at conferences	1 month	Researcher

**Fig. 3 Fig3:**
[figure not shown]
Schedule of enrollment, interventions, and assessments (SPIRIT figure)

### Statistical methods

To assess the homogeneous distribution of confounding variables across the three groups before the intervention, the chi-square test was used for categorical variables, and one-way ANOVA was applied for continuous variables. All analyses will follow the intention-to-treat principle. Missing data (up to 14%) will be imputed using regression methods.

The primary analysis will test the superiority of the interventions on the primary outcome: change in cognitive empowerment score at week 8. To account for multiple comparisons, the significance level for the three pre-planned between-group comparisons (walking vs. control, meditation vs. control, walking vs. meditation) will be adjusted using the Bonferroni correction, resulting in a corrected alpha of 0.0167.

Changes in outcomes over time, between groups, and their interaction will be analyzed using the generalized estimating equation (GEE) model. Baseline individual and clinical variables showing significant between-group differences (e.g., age, marital status, physical activity) will be included as covariates to control for potential confounding. Analyses for secondary outcomes will be considered exploratory.

All analyses will be conducted using Stata version 17, with a two-tailed alpha level of 5% for tests not covered by the primary correction. Graphs will be generated using GraphPad Prism version 8.

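### Missing data are covered only up to 14% although the trial is sized for 20% attrition, and the regression imputation is not identified as single or multiple

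*Protocol article*

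**What the plan says.** The Statistical methods section of the protocol article gives the whole missing-data rule in one sentence: "Missing data (up to 14%) will be imputed using regression methods". It gives no reason for 14% and no rule for a larger share. It does not say whether each gap is filled once or several times, which predictors are used, or how the standard error reflects the imputation. The filled data then go into a GEE. The three between-group comparisons on the primary outcome are "adjusted using the Bonferroni correction, resulting in a corrected alpha of 0.0167".

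The Sample size section uses a different loss figure. It starts from 58 participants, and the reason it gives for enlarging that number is "To account for a possible 20% attrition rate and a design effect of 1.6 due to cluster sampling". Its total is 111, or 37 per arm.

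Two statements in Data collection bear on this. Everyone randomized is to be in the final analysis, and people who stop the sessions are still invited to give outcome data at week 8 and at 3 months.

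**The concern.** The imputation rule ends below the loss that the trial was enlarged to absorb. If missing scores exceed 14%, the article requires all randomized participants in the analysis but names no method for including them. A method chosen at that point would be chosen with the data in view.

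Within the 14%, the result depends on what regression imputation means here. Filling each gap once and analysing the completed data as if fully observed has one of two consequences. With arm in the imputation model, the standard error is too small and the Bonferroni level is not kept. With arm left out, imputed participants carry no treatment effect and the estimate is pulled toward zero. Either would affect the primary comparison.

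**Working it through.** **Inputs from the article.** 58 participants before inflation, design effect 1.6, attrition 20%, final 111 (37 per arm), effect size 0.41, imputation limit 14%, corrected alpha 0.0167.

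**Assumptions not in the article.** Scores are missing completely at random, with the same share m in each arm. The simulations also assume a baseline-to-week-8 correlation of 0.3, 0.5 or 0.7.

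**1. The plan's own figures.**
- Alpha: 0.05 / 3 = 0.0167, as stated. The two-sided critical value is z = 2.394.
- Effect size: 0.8 / √((1.8² + 2.1²)/2) = 0.8 / 1.956 = 0.409, stated as 0.41.
- Final size: 58 × 1.6 × 1.2 = 111.4, stated as 111.

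**2. The two loss figures in participants.**
- 20% of 111 = 22.2, or 7.4 per arm.
- 14% of 111 = 15.5, or 5.2 per arm.
- Because the inflation multiplies by 1.2, the loss that 111 can bear before falling below 58 × 1.6 = 92.8 is 1 − 92.8/111 = 16.4%. That is still above 14%.

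**3. Single imputation with arm as a predictor.** Let σ² be the residual variance and n the arm size.
- *Predicted value only.* The arm mean has true variance σ²/(n(1−m)). The completed data report about σ²(1−m)/n, because imputed residuals are zero and all n are counted. The standard error is too small by the factor (1−m), so the error is 2[1 − Φ(z(1−m))].
  - m = 0.14: z × 0.86 = 2.059, error 0.0395 (2.4 times 0.0167).
  - m = 0.20: z × 0.80 = 1.915, error 0.0555 (3.3 times).
- *Predicted value plus one random residual.* The true variance is (σ²/n)(1/(1−m) + m) and the reported variance about σ²/n. The error is 2[1 − Φ(z/√(1/(1−m) + m))].
  - m = 0.14: 2.394/√1.303 = 2.097, error 0.0360 (2.2 times).
  - m = 0.20: 2.394/√1.450 = 1.988, error 0.0468 (2.8 times).
- At 12% missing the ratios are 2.1 and 1.96, at 10% they are 1.9 and 1.8, and at 5% about 1.4. The error therefore doubles from about 12%.

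**4. Single imputation without arm.** Imputed participants add no arm difference, so the expected estimate is δ(1−m). For δ = 0.41 SD this is 0.41 × 0.86 = 0.35 at 14% and 0.41 × 0.80 = 0.33 at 20%. A simulation at correlation 0.5 gave the same two values. True and reported variance shrink together, so the error stays near nominal.

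**5. Simulation under the null** (37 per arm, robust GEE-type standard error; 6,000 to 16,000 runs, 2,000 for multiple imputation). Ranges run over the settings simulated for each method; a dash means no figure is reported here.

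| Method | Error at 14% missing | Error at 20% missing |
|---|---|---|
| Single, predicted value, arm in model, change score | 0.035–0.044 | 0.041–0.052 |
| Single, predicted value, arm in model, baseline-adjusted | 0.045–0.046 | 0.058–0.063 |
| Single, random residual, arm in model | – | 0.040–0.055 |
| Single, arm not in model | 0.019–0.024 | 0.019–0.024 |
| Multiple (20 sets, Rubin's rules, arm in model, correlation 0.5) | 0.0145–0.0195 | 0.016–0.0165 |

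Complete cases with the same robust standard error gave 0.019 to 0.024, so a small part of the excess in the first three rows is small-sample behaviour and not imputation. For predicted values with arm in the model, the chance of at least one false positive among the three comparisons was 0.088 to 0.116 at 14% and 0.107 to 0.150 at 20%. With multiple imputation it was 0.045 to 0.054. The simulation error of the multiple-imputation figures is √(0.0167 × 0.9833/2000) = 0.003, so they agree with 0.0167.

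**The case against.** A reader might infer that the article prescribes single imputation and therefore more than doubles the error rate. The text does not support that. It never says single, and regression-based multiple imputation, which keeps the error near 0.0167, fits the same words. The doubling also needs arm in the imputation model and roughly 12% or more missing, and the article fixes neither. The number of imputations, the predictors and the combining rules are details that an article may leave to an analysis plan. Their absence alone would be no finding.

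A reader might also infer that 20% of week-8 scores are expected to be missing. That too goes beyond the text. The 20% is an allowance for possible loss. Attrition from sessions need not equal missing scores, because those who discontinue are still invited to the assessments. Loss by 3 months may exceed loss at week 8, where the primary outcome is measured. The 14% could even be meant as the amount anticipated and not as a cut-off, and an analysis plan that is not shown may hold a further rule.

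All of this limits how firmly the point can be put, but does not remove it. On any of these readings the article gives two loss figures and no link between them, and nothing in it ensures that missing scores stay within 14%. Both single-imputation readings of the stated sentence also give a worse analysis than readily available methods.

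**Conclusion.** The concern holds in a conditional form. What the article shows outright is that its imputation rule covers 14% (15 to 16 of 111) while its sample size allows for 20% (about 22 of 111), with all randomized participants to be analysed and nothing stated in between.

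The statistical damage depends on the meaning of the method:
- Single with arm as a predictor: per-comparison error of about 0.036 to 0.040 at 14% missing and 0.047 to 0.056 at 20%, against 0.0167.
- Single without arm: error near nominal, but the effect shrinks by about the missing share.
- Multiple imputation with arm in the model: error near nominal.

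These sizes assume scores missing completely at random and equally across arms, and the simulated ranges further assume correlations of 0.3 to 0.7. The article should be changed because its sentence admits two faulty analyses of the primary outcome and the sound one is cheap to name.

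**What to change.** Remove the 14% limit, or reconcile it with the 20% in the sample size and state what applies above it. Then name the method: multiple imputation with arm, setting (urban or rural), baseline score and the other follow-up score in the imputation model, results combined with Rubin's rules, and the planned GEE fitted to each completed set. If multiple imputation was already intended, saying so settles this part.

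A likelihood-based mixed model for repeated measures fitted to all observed scores, without imputation, is an acceptable alternative. It is a choice and not a necessary replacement of the GEE.

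The cost is a sentence or two in the plan and a little programming in Stata, which the plan already names. Intervals will be somewhat wider than under single imputation with arm as a predictor, because they will then reflect the information that was lost.
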